**Fig. 3 Fig3:**
[figure not shown]
Study population recruitment and randomization strategy

### Concealment mechanism {16b}

The arm allocations will be concealed by keeping this information restricted by the statistician generating the randomizations codes.

### Implementation {16c}

A statistician will generate the randomization codes and an unblinded research team member will package and label the investigational fibers and placebo. These research personnel will not be involved in any other study procedures/assessments. Different research staff will enroll and randomize participants.

## Assignment of interventions: blinding

### Who will be blinded {17a}

Both participants and research team will be blinded to the type of intervention allocated to each arm until the end of the study. The group not on MET (fiber alone) will receive a placebo pill (MCC). The group not on fiber will also receive a placebo (MCC) in identical sachets; this double-blind strategy will reduce risk of bias. Both fiber and MET have a similar side-effect profile, which will support the blinding procedures.

### Procedure for unblinding if needed {17b}

In case of an emergency in which knowledge of the treatment assignment is deemed essential by the participant’s care, the code could be opened. The person in charge of keeping these codes secure will open the code for that specific participant and will inform only the treating physician, keeping the code concealed from research personnel. Any unblinding will be approved by the principal investigator.

## Data collection and management

### Plans for assessment and collection of outcomes {18a}

Study visits will be conducted at the Human Nutrition Research Unit, a state-of-the-art facility supporting leading nutrition intervention research at the UofA. Participants will be seen at baseline (visits 0 and 1), 3, 6, and 12 months, and a phone follow-up will be completed at 1 and 9 months (Table 1). The 12-month duration of the intervention will assess both short- and longer-term effects of the combined FIBER plus MET intervention. At visit 0, and after obtaining informed consent/assent, baseline assessments will be conducted, including demographics, medical history, physical exam, sexual maturation (Tanner stage), anthropometrics, and body composition; in addition, participants will complete QoL, gastrointestinal tolerance, and 7-day physical activity questionnaires. During this visit, research staff will provide to the participants a 3-day food record (to assess dietary intake), Satiety Labeled Intensity Magnitude (SLIM) and bowel habit (Bristol stool chart) questionnaires, and stool sample collection kits to be completed at home and brought to visit 1 (day 0); this visit will occur within the following 10 days after visit 0. At visit 1, fasting blood samples will be withdrawn, and an OGTT will be completed. Once baseline assessments are completed, participants will be randomly assigned to one of the three study groups and the respective study intervention will be delivered.

**Table 1 Tab1:**
[figure not shown]
Time schedule of enrolment, intervention, assessments, and study visits for participants

Abbreviations: *ALT* alanine aminotransferase, *AST* aspartate transaminase, *BUN* blood urea nitrogen, *CBC-D* complete blood count with differential, *GLP-1* glucagon-like peptide 1, *HbA*_*1c*_ hemoglobin A1C, *HOMA-IR* homeostatic model assessment of insulin resistance, *CRP* C-reactive protein, *IL-6* Interleukin 6, *LBP* lipopolysaccharide-binding protein, *PYY* peptide tyrosine tyrosine, *SLIM* satiety labeled intensity magnitude, *TMAO* trimethylamine *N*-oxide, *TNF-α* tumor necrosis factor alpha, *TSH* thyroid-stimulating hormone

Initial assessments, including primary and secondary outcomes, will be repeated at 6- and 12-month follow-up visits. At 1 month, participants will be contacted over the phone to monitor adverse events and compliance. During the 3-month visit, participants will undergo a physical exam and anthropometric assessments and will complete QoL, gastrointestinal tolerance, and SLIM questionnaires, as well as a 3-day food record. At 9 months (phone follow-up), only questionnaires and a 3-day food record will be completed; research staff will assist in completing these questionnaires over the phone when needed (Table 1).

### Demographics and clinical assessment

Date of birth and ethnicity will be collected. A medical history (mode of delivery and infant nutrition practices [breastfeeding or formula], and current medications) will be completed, a physical exam (blood pressure and heart rate using an automated blood pressure monitor) will be conducted, and sexual maturation will be self-assessed (by children assisted by their parents) using the Tanner Stage scale [51].

### Anthropometrics and body composition

After participants void their bladders, body weight and height will be measured and used to calculate BMI percentile and *z*-score (WHO Anthroplus software, Geneva, Switzerland). Waist circumference will be measured in narrowest site between the xiphoid process and iliac crest [52]. Waist circumference *z*-score will be calculated using the Anthropometric Calculator for normal children 5–19 years of age based on the World Health Organization Growth Charts for North America Children [53]. Body density using air displacement plethysmography (Bod Pod® 1SB-060 M, Life Measurement Instruments, CA, USA) [54] will be assessed to estimate fat mass, fat-free mass, and the ratio of fat mass to fat-free mass, according to the manufacturer’s instructions [55].

### Study questionnaires

A 3-day food record (2 weekdays/1 weekend day) will be completed every 3 months to monitor dietary intake and diet quality throughout the study. Self-reported physical activity levels will be assessed every 6 months using the physical activity questionnaire for older children (≤ 14 years) [56] and for adolescents (> 14 years) [57]. QoL will be measured every 3 months using the Peds QL 4.0 instrument [58]. The validated SLIM scale will be used to assess perceived hunger and satiety (fasting, before dinner, and 1 and 2 h after dinner) every 3 months. This scale is a 100-mm visual analog scale anchored by “greatest imaginable hunger” and “greatest imaginable fullness”, with “neither hungry nor full” in the center. Participants will place a mark on the scale corresponding to their sensation of hunger or fullness [59]. To evaluate the gastrointestinal tolerance of the interventions, a previously described gastrointestinal tolerance questionnaire will be used every 3 months [33]. This questionnaire assesses the presence and severity of six symptoms over the previous 7 days, including nausea, gastrointestinal rumblings, abdominal pain, bloating, flatulence, and diarrhea. Participants will rate each symptom as “did not experience,” “no more than usual,” “somewhat more than usual,” or “much more than usual” [33]. Bowel habits will also be recorded over 4 days every 6 months by using a bowel habits diary; in this diary, participants will record bowel movement frequency and fecal consistency rated on a scale of 1 (hard) to 5 (watery) using the Bristol Stool Scale for children [60].

### Assessment of insulin resistance, metabolites, hormones, and intestinal barrier function

As the primary endpoint, HOMA-IR will be calculated as fasting glucose (mmol/L) × fasting insulin (μIU/mL)/22 [61, 62]. HOMA-IR has been shown to be reproducible and correlate with more invasive tests of insulin sensitivity [63, 64]. An OGTT will also be completed and the Matsuda (whole body insulin sensitivity index) [65], insulinogenic [66], and oral disposition [67] indices well be calculated. The OGTT has been validated in multiple clinical and research settings and reflects the efficiency of the body to dispose of glucose after an oral load; it is commonly used to diagnose glucose intolerance and diabetes [68–70]. The participants at risk for T2DM will already require regular screening using OGTT every ~ 6 months; thus, utilizing this gold standard for the study will not create extra patient burden. Participants will ingest 1.75 g/kg (75 g maximum) glucose; blood samples for glucose and insulin will be obtained at 0, 30, 60, and 120 min.

Fasting (12 h) plasma and serum samples will be collected and stored at − 80 °C until further analysis. These analyses include the measure of (1) general safety measures (CBC-D, electrolytes, blood urea nitrogen, creatine, thyroid-stimulating hormone, aspartate transaminase, and alanine aminotransferase), (2) satiety markers (acylated ghrelin, PYY, GLP-1, and leptin), (3) metabolic markers (glucose, insulin, HbA_1c_, total and high-molecular-weight adiponectin, total cholesterol, high-density lipoprotein cholesterol, low-density lipoprotein cholesterol, and triglycerides), (4) inflammatory markers (C-reactive protein, interleukin 6, TNF-α, and lipopolysaccharide-binding protein [LBP; a measure of intestinal barrier function]), and (5) targeted metabolites measured by liquid chromatography–tandem mass spectrometry (amino acids, branched chain ketoacids, acylcarnitines, ceramides, trimethylamine *N*-oxide, choline, and betaine). Protease inhibitors will be added when required for the quantification of hormones.

Fecal samples will also be used to measure calprotectin levels (as a measure of intestinal barrier function) using an enzyme-linked immunosorbent assay according to the manufacturer’s protocol.

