### Outcomes {12}

The primary outcome of this study is a change in IR, as estimated by HOMA-IR, between baseline, 6, and 12 months. The secondary outcomes of this study include changes between baseline, 6, and 12 months in (1) the Matsuda, insulinogenic, and oral disposition indices as determined by OGTT; (2) weight, BMI percentile and *z*-score, and body composition (fat mass, fat-free mass, and ratio of fat mass to fat-free mass); (3) QoL and perceived hunger and satiety; (4) fasting metabolic (glucose, adiponectin, lipids, and OGTT) and satiety markers (acylated ghrelin, PYY, GLP-1, and leptin); (5) measures of systemic inflammation (C-reactive protein, interleukin 6, and TNF-α) and gut barrier integrity (lipopolysaccharide-binding protein [LPB] and fecal calprotectin); and (6) gut microbiome composition and functions (fecal microbiome composition, fecal SCFAs and bile acids, and targeted plasma metabolomics [amino acids, branched chain ketoacids, acylcarnitines, ceramides, trimethylamine *N*-oxide, choline, and betaine]).

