### Participant timeline {13}

#### Sample size {14}

Our primary outcome is IR as estimated by HOMA-IR. Based on a recent study where the effect size of MET on HOMA-IR among pubertal participants was 0.75 [49], we estimated a sample size of 29 per arm, which will give us 90% power to find any significant post-intervention difference between arms at 5% significance level. Additionally, a percentage of change and 95% confidence interval for HOMA-IR after PGX from Pal et al. [50] resulted in an effect size of 0.86, rendering a sample size of 26 per arm. We expect a greater response in the combination therapy; for this reason and considering 26 per arm as feasible, and 15% attrition rate during follow-up, we estimated a total of 90 participants over the 3 arms.

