### Statistical methods

#### Statistical methods for primary and secondary outcomes {20a}

Descriptive statistics will summarize all study variables. Prior to analysis, numerical variables with skewed distribution will be transformed (e.g., log_2_ or cubed root) or a comparable nonparametric test will be used. Between-group comparison of primary and secondary outcomes will be performed at baseline and two consecutive time points independently using unpaired *t*-tests (comparing two groups) or analysis of variance (three groups) and chi-square tests for numerical and categorical data, respectively. Impact of the three interventions on IR (HOMA-IR, primary endpoint) over time will be compared using linear mixed models, after adjusting for relevant confounders, including pubertal stage if any statistically significant difference is observed between treatment groups at baseline. OTU relative abundance will be compared between treatment groups. Statistical analyses for gut microbiota community composition will include principal coordinates analysis and canonical correlation. Linear discriminant analysis Effect Size [78] and multivariate association with linear models will be used to identify specific OTUs that differentiate the treatment groups. Mediation modeling will be employed to provide further insights on possible casual pathways to explore whether the gut microbiota may play a causal or mediation role in the physiological effects detected [79]. Treatment responders versus non-responders will also be evaluated. We will characterize the ecological differences prior to the intervention, and then the individualized response to the intervention in order to assess the role of the microbiome in the host’s metabolic response to the intervention. For this analysis, we will apply a machine learning approach called partition around medoids clustering [80]. Separate models will be estimated for secondary endpoints, which are exploratory, but nevertheless important. Intervention types and times will be included as fixed effects in linear mixed models. Pearson or Spearman correlation coefficients will be computed between changes in gut microbiome composition/function and insulin resistance, hormones, metabolites, and inflammatory markers.

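### The primary-endpoint formula divides by 22 where HOMA-IR in these units is normalised by 22.5: a 2.3% inflation of absolute values, with no effect on the comparison between arms

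*Protocol article*

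**What the plan says.** The section *Assessment of insulin resistance, metabolites, hormones, and intestinal barrier function* introduces HOMA-IR as the primary endpoint and gives its formula: "HOMA-IR will be calculated as fasting glucose (mmol/L) × fasting insulin (μIU/mL)/22". This is the only HOMA-IR formula in the article. The value 22.5 appears nowhere, and no reason is given for a modified index.

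Three other places depend on the quantity or bear on the consequence:

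- *Outcomes {12}*: "The primary outcome of this study is a change in IR, as estimated by HOMA-IR, between baseline, 6, and 12 months".
- *Eligibility criteria {10}*: entry requires a HOMA-IR above 3.16. No formula is given or referred to there.
- *Statistical methods for primary and secondary outcomes {20a}*: before analysis, "numerical variables with skewed distribution will be transformed (e.g., log_2_ or cubed root"), or a nonparametric test is used. The primary comparison over time is by linear mixed models.

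**The concern.** HOMA-IR is a named index with a fixed normalising constant. The units printed in the formula are the ones to which 22.5 belongs, so no change of units turns the constant into 22. The section presents the quantity as ordinary HOMA-IR and relies on that index's reproducibility and its correlation with more invasive tests, so a deliberate variant is unlikely.

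Two things are at stake. The first is the absolute level of the primary endpoint: reported means and changes would not be on the scale a reader expects, and would be slightly out of line with results computed in the usual way. The second is the entry threshold. It is given to two decimals, and its meaning depends on the formula applied to it.

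**Working it through.** **Inputs.** Divisor as written: 22 (formula above). Entry threshold: 3.16 (*Eligibility criteria {10}*). Normalising constant: 22.5. This last figure is not in the article; it is taken as part of the definition of the index in these units (value 1 at glucose 4.5 mmol/L and insulin 5 μIU/mL).

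**1. The constant.** 4.5 × 5 = 22.5. With the divisor 22, the reference point gives 22.5/22 = 1.023 instead of 1.

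**2. Inflation of values and changes.** Let k = 22.5/22 = 1.0227. Each value as written is k times the standard value, an excess of 2.3%. An absolute change is a difference of two such values, so it carries the same factor: k·y₁ − k·y₀ = k·(y₁ − y₀). To go back to the standard scale, multiply by 22/22.5 = 0.978.

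**3. Entry threshold, if screening uses this formula.**

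| | Divisor 22 | Divisor 22.5 |
|---|---|---|
| glucose × insulin must exceed | 3.16 × 22 = 69.52 | 3.16 × 22.5 = 71.10 |
| threshold on the standard scale | 69.52/22.5 = 3.09 | 3.16 |
| insulin threshold at glucose 4.5 mmol/L (assumed) | 15.45 μIU/mL | 15.80 μIU/mL |
| insulin threshold at glucose 5.0 mmol/L (assumed) | 13.90 μIU/mL | 14.22 μIU/mL |
| insulin threshold at glucose 5.5 mmol/L (assumed) | 12.64 μIU/mL | 12.93 μIU/mL |

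The shift runs one way: the formula as written admits people whose glucose × insulin product lies between 69.52 and 71.10, and excludes nobody who would otherwise qualify.

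**4. The comparison between arms.** Multiply every value, in all arms and at all visits, by the same k.

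- Raw scale: differences in means and their standard errors are both multiplied by k, so the test statistic is unchanged.
- Log₂ scale: log₂(k·y) = log₂(y) + log₂(k). The added constant is 0.032; it moves the intercept and cancels from every contrast.
- Cube-root scale: (k·y)^(1/3) = k^(1/3)·y^(1/3). This is again one common factor, so the test statistic is unchanged.
- Rank-based tests: the order of the values does not change.
- Percentage change: (k·y₁ − k·y₀)/(k·y₀) = (y₁ − y₀)/y₀.
- Standardised effect and power: difference and standard deviation both carry k, which cancels. For a standardised effect of 0.75, 90% power and a two-sided 5% level, the normal-approximation sample size is 38 per arm with or without the factor.

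A numerical check on one simulated pair of arms (29 per arm, log-normal values) gave the same t-test p-value with either divisor: 0.1189 on the raw scale and 0.0913 on the log₂ scale.

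**The case against.** The strongest reply concerns sourcing. The article states one formula once, supports it by citations that are not available here, and contains no figure that fails to follow from it. The constant 22.5 comes from outside the document. That is correct as far as it goes, but the constant is part of what the name HOMA-IR means in these units. It is not a result recalled from a particular study.

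A second reply is that this is probably a dropped decimal in a condensed article, and that the full protocol and the database may have the right constant. That is possible and cannot be checked from the article. It limits the weight of the point, but the printed endpoint definition would still need correcting.

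Three stronger readings are tempting, and the document does not support them:

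- *That the error biases or weakens the primary comparison, or does so on the untransformed scale.* It does neither. A common multiplier leaves the planned tests unchanged on every scale the article names.
- *That adolescents below the threshold will be enrolled.* This holds only if screening uses the printed formula. The eligibility section names none, and the formula is introduced as the endpoint, not as a screening rule. Any head count of those affected would also need a distribution of HOMA-IR, which the article does not give. Eligibility is settled before randomisation, so even then the arms would be affected alike.
- *That HOMA-IR values in clinic charts will be mixed with trial values on another scale.* *Recruitment {15}* describes chart review to identify candidates, but does not say that HOMA-IR values from charts enter the trial.

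**Conclusion.** The divisor in the primary-endpoint formula is wrong as printed, and the point stands at minor severity. If the formula is applied as written, absolute HOMA-IR levels and changes are 2.3% too large. The entry threshold of 3.16 corresponds to 3.09 on the standard scale, on the condition that the same formula is used at screening. Between-arm tests, standardised effects, power and percentage changes are unaffected.

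This rests on three assumptions: that the trial means the standard index, with constant 22.5; that one formula is used for all participants and visits; and, for the threshold only, that 3.16 was meant on the standard scale.

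**What to change.** In *Assessment of insulin resistance, metabolites, hormones, and intestinal barrier function*, change the divisor from 22 to 22.5. Confirm that the calculation in the REDCap database uses 22.5. In *Eligibility criteria {10}*, state that HOMA-IR is computed by the same formula.

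The cost is one constant, one check of the database and one added sentence. *Trial status* reports that recruitment had not started at this version, so no data needed recalculation then. Had values since been computed with 22, multiplying them by 22/22.5 would restore the standard scale exactly. The sample size and analysis model need no change on this account.

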### Fecal microbiome analyses

Once collected from participants, stool samples will be immediately processed, aliquoted, and stored at − 80 °C until further analysis. DNA will be extracted from the fecal homogenates using the QIAamp DNA Stool Mini Kit (Qiagen, Valencia, CA, USA) with the addition of a mechanical lysis step, as recently described by Costea et al. [71]. Fecal microbiota composition will be characterized by 16S rRNA gene amplicon sequencing using MiSeq Illumina technology (pair-end) as previously described [33]. Quality-controlled reads will be analyzed using (1) taxonomic-based approaches (GAST and the Ribosomal Database Project Multi Classifier tool) and (2) non-taxonomic-based clustering algorithms for operational taxonomic unit (OTU) determination with the UPARSE pipeline. α-diversity (Shannon, Simpson, and observed OTUs) and β-diversity indices (Bray-Curtis and binary Jaccard) will be calculated in QIIME2 [72] and R (VEGAN package) [73]. To assess metabolic functions of the gut microbiota, fecal SCFAs will also be analyzed by gas chromatography (Varian, CA, USA) [74] and bile acids using liquid chromatography–mass spectrometry [75, 76].

### Plans to promote participant retention and complete follow-up {18b}

When a participant expresses his/her wishes to withdraw from the study, he/she will be asked to complete an “end of study” visit. Data collected up to the time of withdrawal will remain in the trial database and be included in data analysis, unless otherwise indicated by the participant.

### Data management {19}

Study charts will be stored within a secure cabinet at site. All research data will be captured and managed using Research Electronic Data Capture (REDCap) [77] hosted at the Faculty of Medicine and Dentistry at the UofA. To ensure data quality, the database will be designed with branching logic, data validation, and range checks for data values, where possible. Research data and study documentation will be retained for a period of 25 years.

### Confidentiality {27}

No directly identifying information will be entered in the REDCap system, and participants will be identified by a unique participant study number (code) on the case report forms. Personnel entering research data into REDCap will have a personal username and password after access has been granted by the REDCap administrator. This password will be required to be changed periodically. Other study-related documents containing direct identifiers (e.g., signed consent form) will be stored in a locked filing cabinet in a secure office at site. All computer files related to this study (e.g., master list and data set) will be encrypted and password protected. Participants will be informed during the consent inform process that the coded research data and original medical records may be inspected by UofA auditors, members of the Research Ethics Board, and Health Canada, for regulatory and monitoring purposes.

